#### Statistical power

For aim 1, under regular settings (power>80%, 2-sided *p*-value<.05), we can detect a medium effect size of 0.46 times standard deviation (*SD*) on penetration when the covariates have no effect, and a medium effect size of 0.40 times *SD* when the covariates explain 20% of the variance in penetration. The power for moderation analysis is weaker and more difficult to quantify; in a simplified setting of high versus low values, we can detect a large moderation effect size of 0.89 times *SD*.

Under the same settings for aim 2, if we suppose that across all patterns each treatment organization can provide two measurements over time, on average, and assume an intra-class correlation no greater than 0.40, we can detect a small standardized effect size of 0.34 times *SD*. Based on guidelines for mediation analysis [107], we can detect a moderately small mediation relationship (i.e., standardized *μ*^(0)^=0.26) by most methods drawing inference for the indirect effect, when the intra-class correlation is no bigger than 0.50. In a simplified setting of high vs. low values in a moderator, we can detect a medium moderation effect size of 0.69 times *SD*.

#### Sensitivity analyses

Sensitivity analyses will account for observed and unobserved secular trends, using the same models for penetration and sustainment. First, we will test non-equivalent-dependent variables (medication treatment variables) as *Y*^*N*^ outcomes, moderators during the grant funding period (aim 1a) or in each year of sustainment (aim 2a). We hypothesize grant type will not have significant effects on non-equivalent dependent variables, but if we find one, we will adjust the standardized effect size for the relevant outcome (penetration or sustainment) by subtracting out the effect size for the non-equivalent dependent variable. Second, we will repeat all primary analyses controlling for each organizations’ years of active funding (time fixed efforts), which could capture unobserved secular trends missed by our non-equivalent-dependent variables. If grant effects are reduced by controlling for time, we will use our qualitative data to help understand why.

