#### Measures for sensitivity analyses

To help understand trends that may be confounded with grant type in our quasi-experimental design, we will conduct a series of sensitivity analyses. We will account for non-secular trends by creating a series of binary variables (using CHS records) that indicate which years each state had active SAMHSA state-focused grant support. To account for secular trends, we will collect non-equivalent dependent variables [91, 92] from publicly available data about the participating treatment organizations. Non-equivalent dependent variables are uniquely useful when comparing groups exposed to different policy interventions in non-overlapping time periods with no control groups available. These variables capture an observed secular trend because they (1) *are not* expected to be influenced by the predictor variable of interest (i.e., grant type) but (2) *are* expected to be influenced by factors that provide an alternate explanation for observed differences (i.e., other factors that could promote EBP implementation at SUD treatment organizations).

The non-equivalent dependent variable design is strengthened by the inclusion of multiple variables, each with controlled covariates. At a minimum, we plan to examine variables representing organization-level use of medication treatments for opioid use disorder (e.g., methadone detoxification/maintenance, buprenorphine use) as non-equivalent dependent variables; each represents a discrete EBP that could be influenced (as with A-CRA) by efforts to improve substance use care, but not by A-CRA-focused grants. We will collect each variable from the publicly available National Survey of Substance Abuse Treatment Services (N-SSATS) [93], an annual census of SUD treatment organizations (since 2000; response rates ≥90%), and control for increases in state-level (a) opioid-related overdose death rates among adults using CDC cause of death data [94] and (b) SAMHSA grant funding amounts for opioid-specific treatment services [95]. We will also continue exploring N-SSATS data to identify other candidate non-equivalent dependent variables, each of which would require its own set of covariates. We will collect all variables for every year relevant to our analyses; i.e., 2009 (when the first organization-focused grants ended) through 2025 (our final year of data collection).

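### The secular-trend correction is made only when the non-equivalent dependent variable test is significant, so a moderate trend is often left in and otherwise over-corrected

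*Protocol article*

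**What the plan says.** The Sensitivity analyses section of the protocol article fits the NEDVs as outcomes, "using the same models for penetration and sustainment". It expects no significant grant-type effect on them and then gives a conditional rule: "if we find one, we will adjust the standardized effect size for the relevant outcome (penetration or sustainment) by subtracting out the effect size". The amount subtracted is the NEDV's own standardized effect. A second analysis in the same section repeats the primary analyses with time effects for years of active funding.

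Measures for sensitivity analyses says what the NEDVs are: "At a minimum, we plan to examine variables representing organization-level use of medication treatments for opioid use disorder". They come from an annual census of treatment organizations, more than one is intended, and each has its own covariates.

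Statistical power gives the only figures on precision. For aim 1, "we can detect a medium effect size of 0.46 times standard deviation" with no covariate effect, at power above 80% and two-sided 5%. For aim 2 the figure is 0.34 SD. No power is stated for the NEDV tests. Quantitative data analysis refers the equations to Additional file 4, which is not part of the material reviewed.

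**The concern.** The two grant programmes ran in different years, so a secular trend is the obvious rival explanation for any difference between them. The NEDV comparison is the article's main quantitative protection against it.

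Correcting only after a significant test makes this a pre-test procedure, which has two known weaknesses. When the test misses a real trend, nothing is subtracted. When it detects one, the NEDV estimate that passed the threshold is on average too large, so too much is subtracted. A reader of the final report could take an uncorrected estimate as cleared of secular trend when the NEDV test merely lacked power.

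**Working it through.** **Inputs.** About 85 and 82 organizations (Abstract, Method); detectable effects 0.46 and 0.34 SD (Statistical power); the conditional rule (Sensitivity analyses).

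**Protocol figures first.** Detectable effect = (1.96 + 0.84) × SE.
- Aim 1: SE = √(1/85 + 1/82) = 0.155, so 2.80 × 0.155 = 0.434 SD, against 0.46 stated.
- Aim 2, two measurements at intra-class correlation 0.40: variance factor (1 + 0.40)/2 = 0.70, so 0.434 × √0.70 = 0.363, against 0.34 stated. With 20% of variance explained, 0.363 × √0.80 = 0.325.

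The stated figures are not reproduced exactly. The clustering and response assumptions behind them are not given, so no error is alleged. The rest uses the protocol's own values: SE = 0.46/2.80 = 0.164 (aim 1) and 0.34/2.80 = 0.121 (aim 2).

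**Assumptions added here.** There is one NEDV, its effect has the same SE as the A-CRA effect, the trend b is equal in both outcomes, there is no true grant effect, and the sampling correlation ρ between the two estimates is 0, 0.3 or 0.5. The article gives neither b nor ρ.

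**Chance that the trend is flagged**, Φ(b/SE − 1.96):
- Aim 1, b = 0.30: Φ(1.83 − 1.96) = 45%.
- Aim 2, b = 0.30: Φ(2.47 − 1.96) = 70%; b = 0.20: Φ(1.65 − 1.96) = 38%.

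**Bias in each branch (aim 1, b = 0.30, ρ = 0).** Unflagged studies (55%) keep +0.30. In flagged studies (45%) the NEDV estimate averages 0.445, so subtraction leaves 0.30 − 0.445 = −0.145. Overall: 0.553 × 0.30 − 0.447 × 0.145 = 0.10 SD. At ρ = 0.5 the branches average +0.24 and −0.07.

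**False positives, simulated.** Whenever subtraction occurs, the adjusted effect is tested with the correct SE of the difference, SE × √(2(1 − ρ)), so the excess comes from the trigger alone.

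| Aim, b | Flagged | No correction | Planned rule, ρ = 0 / 0.3 / 0.5 |
|---|---|---|---|
| 1, 0 | 5% | 5% | 6 / 6 / 5% |
| 1, 0.20 | 23% | 23% | 20 / 17 / 14% |
| 1, 0.30 | 45% | 45% | 27 / 22 / 19% |
| 1, 1.00 | 100% | 100% | 5 / 5 / 5% |
| 2, 0.20 | 38% | 38% | 26 / 21 / 18% |
| 2, 0.30 | 70% | 70% | 24 / 20 / 17% |

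The second and third columns agree because both tests are given the same SE and shift. If the SE were left unchanged after subtraction, aim 1 would give 33 / 25 / 19% at 0.30 SD and 8 / 6 / 5% with no trend.

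**Alternative.** Always subtracting, with the SE of the difference, gives 5% at every trend size when the shifts are equal. If the NEDV carries only half the shift (aim 1, b = 0.30, ρ = 0), it gives 9.9%, against 39% for the planned rule.

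**The case against.** Several points on the other side stand.

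- **It is a labelled sensitivity analysis.** A time-effects analysis follows it for trends the NEDVs miss, qualitative follow-up is planned if grant effects shrink, and the article disclaims isolating a causal effect. This lowers the severity.
- **The planned rule helps at moderate trends.** At 0.30 SD for aim 1 it gives 19-27%, or 19-33% if the SE were unchanged, against 45% with no correction. Most of the error comes from confounding, not from the rule.
- **The power of the NEDV test is assumed.** The NEDVs come from yearly census data, have their own covariates, and number more than one. The chance of flagging at least one could exceed the figures above. More flags would not remove the over-correction that follows from selecting on significance, and chance flags would become more common too.
- **The article does not say that the adjusted effect will be re-tested.** The false-positive rates describe what a reader testing it at 5% would meet.

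A reader might also infer that the adjusted effect carries no uncertainty and that its intervals will be too narrow. The article does not support this. It states no variance for the adjusted effect, but the equations are in Additional file 4, so silence here is not an error. Nor can one infer that false positives exceed 5% by a wide margin in general. They are 5-8% with no trend and return to 5% for a large trend when the correct SE is used.

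**Conclusion.** The concern holds in a limited form. The rule written in the article makes the correction depend on a significant NEDV test and so reads non-significance as absence of trend. By the protocol's own precision, and if the NEDV test is similarly precise, a 0.30 SD trend would go uncorrected in about 55% of studies for aim 1 and 30% for aim 2; where it is corrected, the correction is on average too large.

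False-positive rates of 19-27% (aim 1, 0.30 SD) and 18-26% (aim 2, 0.20 SD) follow from the trigger alone, whatever Additional file 4 says about variance. They depend on a moderate trend of equal size in both outcomes and on correlations between 0.5 and 0, none of which the documents fix. This is a worthwhile, inexpensive improvement to a sensitivity analysis and does not call the primary model into question.

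**What to change.** Drop the significance trigger. For each primary outcome, report two effects side by side whatever the NEDV p-value:
1. the unadjusted grant-type effect, which remains primary;
2. the NEDV-adjusted effect, with a confidence interval for the difference between the A-CRA and NEDV effects, from a bootstrap that resamples states or from a joint model of both outcomes.

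Full subtraction is unbiased only if the NEDV carries the same shift as the A-CRA outcome. So also show the adjusted effect when k times the NEDV effect is subtracted, with k = 0, 0.5 and 1 as the assumed ratio of the A-CRA shift to the NEDV shift. Add k = 2 if the NEDV may carry only half the A-CRA shift. State in advance whether several NEDVs are used singly or averaged, and say where the variance of the adjusted effect is defined.

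**Cost.** Analysis-plan wording and a bootstrap or joint fit; no new data. The loss is precision. At k = 1 the interval widens by √(2(1 − ρ)), which is 1.41 at ρ = 0 and 1.18 at ρ = 0.3. The aim 1 detectable effect for the adjusted analysis becomes 0.46 × 1.41 = 0.65 SD or 0.46 × 1.18 = 0.54 SD. The primary analysis keeps its stated power.

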#### Quantitative data analysis

We will integrate the data collected in this project with our prior data [33, 34, 48]. To compare state-focused vs. organization-focused grants, we will fit hierarchical models for penetration outcomes (aim 1) and longitudinal pattern-mixture models [101, 102] for sustainment outcomes (aim 2). Variables in the model come from two levels, state and organization, with ratings from multiple respondents averaged to the organization level (as in the previous project). In aim 2, each organization will have up to four repeated measurements, allowing us to fit organization-specific trajectories. Longitudinal pattern-mixture models do not require fully synchronized measurements across organizations, which is suitable for our analyses. We will have missing data at some measurement points due to nonresponse and the timing of data collection (see Table 1), so we will apply multiple imputation [103] and data reweighting [104] to handle nonresponse. If organizations differ significantly on observable characteristics and baseline outcomes, the model fitting process will use propensity scores [105] to adjust for covariate balancing. These models can be readily fit in the general statistical software package SAS 9 PROC MIXED. After fitting all models, we will apply the step-up method [106] to adjust for multiple comparisons and maintain a type I error rate <0.05 for each aim. For analyses of mechanisms, we will examine moderators by adding interaction terms to the models and will use structural equation models to examine indirect and direct mediation effects; for aim 2, the moderator and mediator variables are time-varying. Additional file 4 presents detailed equations for each analysis in aims 1 and 2.

We hypothesize that treatment organizations implementing A-CRA under state-focused grants will have higher penetration rates compared to organization-focused grantees, with differences between grant types moderated by external support and leadership quality. Similarly, we predict that state-focused grants will show greater A-CRA sustainment by treatment organizations across 5 years post-funding, with moderation by leadership quality and sustainment capacity mediation by changes in external support and funding stability over time.

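### The secular-trend correction subtracts the control variable's standardized effect at full weight, which assumes without support that the trend moves medication use and A-CRA outcomes by equal SDs

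*Protocol article*

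**What the plan says.** The Sensitivity analyses section of the Protocol article tests grant type against non-equivalent dependent variables, "using the same models for penetration and sustainment". No effect is expected, but "if we find one, we will adjust the standardized effect size for the relevant outcome (penetration or sustainment"), and this is done "by subtracting out the effect size for the non-equivalent dependent variable". So the rule is triggered by significance, works on the SD scale and has an implied coefficient of 1.

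The Measures for sensitivity analyses section names the control variables as "variables representing organization-level use of medication treatments for opioid use disorder", for example methadone or buprenorphine. The reason given is that "each represents a discrete EBP that could be influenced (as with A-CRA) by efforts to improve substance use care", while A-CRA grants should not affect them. The analysis will also "control for increases in state-level (a) opioid-related overdose death rates among adults" and for opioid-specific SAMHSA funding. Neither the coding nor the prevalence of medication use is given.

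The outcomes being corrected are on other scales. Penetration is a proportion of providers certified, and sustainment is a 0 to 10 composite (Outcomes section). On the models, the Quantitative data analysis section says: "These models can be readily fit in the general statistical software package SAS 9 PROC MIXED".

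**The concern.** A non-equivalent dependent variable shows whether something other than the grants was changing between the two eras. To use it as a numerical correction takes one more assumption: how far the A-CRA outcome would have moved for each SD by which the control variable moved. Subtraction at full weight fixes that ratio at exactly 1. The stated rationale supports a shared source of influence. It says nothing about equal size on three differently scaled variables.

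If the true ratio is below 1, the rule removes too much and can hide a real difference between grant types. If it is above 1, the rule removes too little and leaves era bias in a figure presented as corrected. The two grant programmes were awarded in different years (2006–2010 and 2012–2017, Project context section), so readers are likely to rely on the corrected figure when they judge whether a grant-type difference is more than a difference between eras.

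**Working it through.** **Inputs from the documents.** About 85 state-focused and 82 organization-focused organizations (Abstract); detectable effects of 0.46 SD (Aim 1, no covariate effect) and 0.34 SD (Aim 2), with power above 80% and two-sided 0.05 (Statistical power section).

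**Assumptions of this check.** The control variable is estimated with about the same precision as the outcome. For step 4 only, medication use is coded yes/no.

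**1. The plan's own yardstick.** SE = sqrt(1/82 + 1/85) = 0.155 SD. Detectable effect = (1.96 + 0.84) x 0.155 = 0.434 SD. The stated 0.46 is slightly larger. It would follow from 75 organizations per group or from a variance inflation of about 1.125 (0.434 x sqrt(1.125) = 0.46). This is not called an error; 0.46 serves only as a measure of size.

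**2. Smallest correction that can be triggered.** A control effect is significant when it exceeds 1.96 x 0.155 = 0.30 SD. Any Aim 1 correction is therefore at least about 0.30 SD, or 0.30/0.46 = 65% of the detectable effect. For Aim 2, scaling the stated 0.34 by 1.96/2.80 gives about 0.24 SD.

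**3. Effect of the weight.** Let b be the true shift in the A-CRA outcome, in SD, per SD of shift in the control variable. Then:

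- correct adjusted effect = d - b x d(control)
- bias left by the plan's rule = (b - 1) x d(control)

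With d = 0.46 and d(control) = 0.30:

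| b | Correct adjusted effect (SD) | Bias left by weight 1 (SD) |
|---|---|---|
| 0 | 0.46 | -0.30 |
| 0.5 | 0.46 - 0.15 = 0.31 | -0.15 |
| 1 | 0.46 - 0.30 = 0.16 | 0 |
| 2 | 0.46 - 0.60 = -0.14 | +0.30 |

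The point estimate reaches zero at b = 0.46/0.30 = 1.53. With an interval for the difference, SE = 0.155 x sqrt(1 + lambda² - 2 x lambda x r), where r is the correlation of the two estimates. The lower 95% limit then reaches zero earlier:

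- r = 0, lambda = 0.43: 0.46 - 0.129 = 0.331, and 1.96 x 0.155 x sqrt(1 + 0.185) = 0.33.
- r = 0.5, lambda = 0.65: 0.46 - 0.195 = 0.265, and 1.96 x 0.155 x sqrt(1 + 0.4225 - 0.65) = 0.27.

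In this example the conclusion turns on a weight between 0 and 1, which the plan does not examine.

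**4. Prevalence, if coding is yes/no.** d = (p2 - p1)/sqrt([p1(1 - p1) + p2(1 - p2)]/2). For the same rise of 10 percentage points:

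| Rise | Pooled SD | d (SD) |
|---|---|---|
| 45% to 55% | 0.497 | 0.20 |
| 20% to 30% | 0.430 | 0.23 |
| 10% to 20% | 0.354 | 0.28 |
| 5% to 15% | 0.296 | 0.34 |

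Only the last passes the Aim 1 trigger of about 0.30. For a constant odds ratio of 2 the pattern reverses: 0.18 SD from a 5% base and 0.34 SD from a 50% base. Either way, the size of the correction depends partly on how common medication use is.

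**5. The covariates.** Adjusting for overdose deaths and opioid funding may bring d(control) closer to the general trend. It changes the value of d(control), but it does not estimate b.

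**The case against.** The strongest reply is that this is a conditional sensitivity analysis in a study that expressly does not aim to isolate the causal effect of grant type (Current project section). The primary estimate and test are untouched. The plan intends several control variables, each with its own covariates, and a second analysis with time fixed effects for trends that the control variables miss. The unadjusted and adjusted results already correspond to weights 0 and 1. Additional file 4, which holds the equations, is not shown and may specify coding and standardization.

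Much of this stands, and it limits how serious the point is. It does not supply the missing argument: neither covariates nor further control variables show that the trend moves both outcomes by equal SDs, and the article states the subtraction as a rule.

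A reader might infer more than the documents support:

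- **That prevalence largely drives the correction.** This needs yes/no coding and a low base rate, and neither is stated. Between bases of 20% and 50%, a 10-point rise changes only from 0.23 to 0.20 SD.
- **That a modest trend could yield a correction near or above 1 SD.** Such figures come from a logit-based effect size (1.05 for 2% to 12%). The plan applies the same models as for the main outcomes and names a linear mixed-model procedure.
- **That this is the plan's main defence against era confounding.** No section ranks it so, and the time-fixed-effects analysis stands beside it. That analysis may separate era from grant type poorly, because the award years differ, but it is part of the plan.
- **That the opioid-specific drivers show the control variables to be unsuitable.** The article names overdose deaths and opioid funding because it will adjust for them.

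**Conclusion.** The concern holds. Full-weight subtraction is unbiased only under equal SD shifts, which the Protocol article neither states nor supports. In the worked example the adjusted effect runs from 0.46 to -0.14 SD over weights 0 to 2, and is 0.16 SD under the plan's rule. These figures assume similar precision for control and outcome, and take the plan's detectable effect as the observed one; they illustrate the size and are not a forecast. The dependence on prevalence (0.20 against 0.34 SD for the same 10-point rise) is a secondary point and rests on yes/no coding. What is at risk is the reading of the adjusted sensitivity estimate, not the primary comparison.

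**What to change.** In the Sensitivity analyses section, replace the single one-for-one subtraction with d - lambda x d(control), reported over a range of lambda that includes 0 and 1. Give an interval at each lambda that carries the uncertainty of both effects and their correlation, for example from a joint bootstrap. Report the lambda at which the conclusion changes, and say in words what that value means: how strongly the A-CRA outcome would have to follow the trend seen in medication use. State the equal-shift assumption next to the lambda = 1 result.

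Moving both variables to a percentage-point scale is not a substitute, because it replaces one untestable equal-shift assumption with another.

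The cost is revised wording and a short table; no new data are needed. The downside is that the result is a range and not one corrected number.

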### Project context

As noted earlier, SAMHSA has used both organization-focused and state-focused discretionary grant strategies to fund EBP implementation (including A-CRA) for adolescent SUD. All grants were administered by SAMHSA’s Center for Substance Abuse Treatment [59], whose primary role was to provide funding, oversight, and national leadership to grantee organizations and states/territories/tribal entities (hereafter, “states”). SAMHSA funded (i) four cohorts of organization-focused grantees, awarded 2006–2010, across 26 states followed by (ii) four cohorts of state-focused grantees, awarded 2012–2017, across 22 states. Eight states had recipients of both grant mechanisms, so overall, 40 states were represented across cohorts.

In both initiatives, SAMHSA partnered with Chestnut Health Systems (CHS; an organization that conducts A-CRA training and research) to provide training and certification for A-CRA clinicians and supervisors. CHS provided a standardized, 2.5-day training for all organization-focused grantees and most clinicians in state-focused grantees’ states—although some received training from certified A-CRA supervisors. In every case, CHS still oversaw A-CRA clinician and supervisor certification. Certification activities required each trainee to demonstrate competency in delivering A-CRA treatment and/or supervision procedures, depending on their role. Specifically, clinicians and supervisors participated in twice monthly, group-format coaching calls with CHS expert consultants; they also submitted audio-recorded A-CRA therapy or supervision sessions, respectively, and their consultant provided numeric ratings and written feedback [60–62]. Typically, the certification process lasted from 6 months to a year.

Next, we describe the two grant types in more detail. We follow recommendations for specifying implementation strategies in terms of actors, actions, action targets, temporality, dose, outcomes, and justification [27, 36].

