#### Organization-focused grants

SAMHSA awarded these grants directly to treatment organizations. Grantees received ~$900,000 across a 3-year period to support A-CRA implementation. These grants targeted the EPIS inner context by paying for clinicians delivering A-CRA, supervisors providing A-CRA supervision, and related activities such as evaluation (see https://externallinks.samhsa.gov/grants/2009/ti_09_002.dhtml to view a representative request for proposals). Our prior work showed that grantees generally had initial success in implementing A-CRA with fidelity and reducing youth substance use, but many did not sustain A-CRA post-funding [32–34].

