#### State-focused grants

SAMHSA awarded these grants to state agencies that administer publicly funded SUD services. These were ~$3–4 million, 3- to 4-year awards (sometimes extended to 6 years) that could support the implementation of several EBPs; most funded states selected A-CRA. The grants targeted EPIS outer context factors [4, 43, 63]—one third of the grant funds paid for states to develop EBP-focused infrastructure like funding, training, developing policies, and promoting treatment organizations’ capacity to deliver youth SUD treatment. State agencies proposed up to six “dissemination site” organizations that implemented A-CRA first; those sites received funds similar in amount and purpose to those provided to organization-focused grantees, thus still addressing inner context factors. See https://www.samhsa.gov/grants/grant-announcements/ti-17-002 to view a representative request for proposals. The outcomes of state-focused grants have not been evaluated.

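### Funding-year fixed effects cannot separate the grant effect from a between-era shift: on the article's own dates, grant type is a linear combination of the year indicators

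*Protocol article*

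**What the plan says.** Under Sensitivity analyses, the second check repeats every primary analysis controlling for each organization's "years of active funding (time fixed efforts), which could capture unobserved secular trends missed by our non-equivalent-dependent variables". If the grant effect shrinks once time is controlled, the team will turn to the qualitative data for an explanation.

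Under Measures for sensitivity analyses the variable is different: a series of "binary variables (using CHS records) that indicate which years each state had active SAMHSA state-focused grant support". It is defined per state and for state-focused support only, and it is assigned to non-secular trends. The same section justifies the non-equivalent dependent variables as suited to "comparing groups exposed to different policy interventions in non-overlapping time periods with no control groups available".

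The dates come from three places:
- Project context: "four cohorts of organization-focused grantees, awarded 2006–2010, across 26 states", followed by "four cohorts of state-focused grantees, awarded 2012–2017, across 22 states".
- The two grant descriptions: "Grantees received ~$900,000 across a 3-year period to support A-CRA implementation" for organization-focused grants, and "3- to 4-year awards (sometimes extended to 6 years") for state-focused ones.
- Table 1: the three eligible state-focused cohorts are 2013-2017 (37 organizations), 2012-2018 (33) and 2017-2021 (21).

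The model equations are in Additional file 4, which is not shown.

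**The concern.** The two grant types belong to different eras. A 3-year award made in 2010 ends in about 2013, and most state-focused funding comes after that. A fixed effect for each funding year lets the outcome level differ freely by year. If the years that were funded already tell the model which grant an organization held, nothing remains from which to estimate a grant effect.

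The secular-trend plan has two quantitative parts, and this is the only one aimed at unobserved trends. If the grant effect is aliased, the software drops a column or returns one of many equivalent solutions. An apparent reduction after controlling for time would then depend on that choice. The planned qualitative follow-up would be explaining a numerical artefact, and the findings go on to inform the Aim 3 policy brief.

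**Working it through.** The article states no figure for this analysis, so there is none to reproduce. The check is whether grant type adds rank to a model that already contains the time terms.

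**Inputs.** State-focused cohorts and sizes are from Table 1. Organization-focused awards run 2006-2010 in four cohorts of 3 years each. The two middle award years are not given, so all three choices from 2007, 2008 and 2009 were tried, with 2006 and 2010 fixed. The 82 organization-focused organizations (Abstract) are split equally over the cohorts; this is an assumption and affects only the weights.

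**1. Year fixed effects.** Let I(y) = 1 if the organization was funded in year y.

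| Cohort | I(2017), end year counted | I(2016) + I(2018), end year not counted |
|---|---|---|
| Organization-focused, all (end by about 2013) | 0 | 0 + 0 = 0 |
| State 2013-2017 | 1 | 1 + 0 = 1 |
| State 2012-2018 | 1 | 1 + 0 = 1 |
| State 2017-2021 | 1 | 0 + 1 = 1 |

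Each right-hand column equals the grant-type variable. In matrix form, an intercept plus the 2006-2021 indicators has rank 7, and adding grant type leaves it at 7. This holds for all three choices of middle award years, with end years counted or not. Award-year dummies and end-year dummies give the same 7 and 7.

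The result does not hang on the assumed organization-focused pattern. Allowing every award year 2006-2010 with lengths of 2 to 5 years gives rank 14 without and 14 with grant type (end years counted), and 13 and 13 (not counted). The overlap in active years around 2012-2013 does not help, because the later indicators already reproduce grant type.

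**2. Codings that are estimable.** VIF = 1/(1 - R²), where R² is from regressing grant type on the time terms. The standard error grows by √VIF.

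| Time term | Rank without, with grant type | VIF | SE multiplier |
|---|---|---|---|
| Linear award year | 2, 3 | 3.3-3.8 | 1.83-1.95 |
| Quadratic award year | 3, 4 | 3.7-4.5 | 1.92-2.12 |
| Linear end year | 2, 3 | 6.4-7.2 | 2.52-2.67 |
| Funding duration | 2, 3 | 2.5 | 1.59 |

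Example, linear award year with awards in 2006, 2007, 2009 and 2010:
- Mean award year is 2008.00 (organization) and (37×2013 + 33×2012 + 21×2017)/91 = 2013.56 (state), a gap of 5.56 years.
- Between-type sum of squares: (82×91/173)×5.56² ≈ 1334. Within-type: 82×2.5 + 340.4 ≈ 545.
- R² = 1334/(1334 + 545) = 0.71, VIF ≈ 3.4, √VIF ≈ 1.86.

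Linear and quadratic terms identify the grant effect by carrying a fitted trend across award eras that do not overlap. Duration is 3 years for every organization-focused cohort and 4, 6 and 4 years for the Table 1 cohorts, so it also extrapolates, and it does not measure calendar time.

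The state-level indicators give rank 4 and 4 if no organization-focused grantee lies in a state with a state-focused grant. They give 4 and 5 once one grantee lies in a state from an eligible cohort. The article says "Eight states had recipients of both grant mechanisms", so this coding is probably estimable, but only through those grantees. For Aim 1 it would mostly mark years after their own grant had ended.

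**3. Drift needed to explain an effect.** The state-focused mid-grant year is (37×2015 + 33×2015 + 21×2019)/91 = 2015.92. The organization-focused one is the mean award year plus 1.5, which is 2009.25 to 2009.75. The gap is 6.2 to 6.7 years. The Aim 1 detectable effect of 0.46 SD then corresponds to 0.46/6.7 = 0.069 to 0.46/6.2 = 0.074 SD per year.

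**The case against.** The strongest reply is that the article does not settle the coding. Its only definition of the variable is the state-level set of binary indicators, and under that coding the grant effect is estimable through the dual-grant states. Additional file 4 may specify something else again. This stands, and it limits the claim of non-identification to literal year fixed effects.

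Two further doubts concern the funding patterns. Award lengths could differ within a state-focused cohort, which might break the identity for active-year or end-year dummies; it would not for award-year dummies, because award years do not overlap between types. An organization-focused grantee might also have received state-focused support later, since the article states an exclusion only for organizations whose two grants were active together. Any identification gained that way would rest on a small, unusual group.

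The article also discloses the non-overlapping periods, disclaims causal isolation of grant type, and sends a reduced effect to qualitative interpretation rather than to a changed conclusion. That lowers the severity. It does not make the adjusted estimate interpretable.

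A reader might infer more than the documents support:
- That funding year is fixed by grant type. It varies within each type; the dependence runs from the year indicators to grant type.
- That the analysis cannot be run at all. Several codings are estimable.
- That no secular trend can be examined. Trends across cohorts within a grant type remain estimable.
- That the separate calendar periods of Aim 2 measurement prove the aliasing. The planned control is years of active funding, which is a different covariate.

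**Conclusion.** The point holds in this limited form. With year fixed effects taken literally, grant type is an exact linear combination of the funding-year indicators and the adjusted grant effect is not identified. With the other codings it is estimable, but by extrapolation or through dual-grant states, so none separates the grant effect from an unrestricted shift between eras. The rule on grant effects that shrink after controlling for time cannot be read as intended.

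The aliasing rests on Table 1's dates applying uniformly within each cohort and on no organization-focused grant being active from 2016 onward. The VIF and drift figures rest additionally on the assumed middle award years and equal organization-focused cohort sizes. Separately, the two sections define the time variable differently and assign it to opposite kinds of trend, which is visible whatever the coding.

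This is a should-fix, because it affects a sensitivity analysis. Confidence is moderate, because Additional file 4 is not shown.

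**What to change.** 1. Do not use funding-year fixed effects as the check on the grant effect.
2. Replace them with a linear award-year slope common to both grant types, estimated from cohort-to-cohort variation within each type. Report it as resting on linearity across eras.
3. Add a tipping-point analysis: the annual secular drift that, multiplied by the gap in mid-grant year, would account for the estimated grant effect. The benchmark above is about 0.07 SD per year for 0.46 SD.
4. Reconcile Measures for sensitivity analyses with Sensitivity analyses: one definition of the time variable, its unit (state or organization), its coding, and the kind of trend it addresses. Align Additional file 4 with it.

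The cost is wording in the analysis plan, with no new data. The price is precision: the standard error is about 1.9 times larger, so an effect of 0.46 SD detectable without the slope becomes roughly 0.46 × 1.9 = 0.87 SD with it. The common slope also extrapolates, so it should stay a sensitivity analysis and be read beside the tipping point.
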